## Abstract

**Background:**

A large proportion of the Danish population consumes more than the officially recommended weekly amount of alcohol. Untreated alcohol use disorders lead to frequent contacts with the health care system and can be associated with considerable human and societal costs. However, only a small share of those with alcohol use disorders receives treatment. A referral model to ensure treatment for alcohol dependent patients after discharge is needed. This study evaluates the i) cost-effectiveness ii) efficacy and iii) overall impact on societal costs of the proposed referral model - The Relay Model.

**Method/Design:**

The study is a single-blind pragmatic randomized controlled trial including patients admitted to the hospital. The study group (*n* = 500) will receive an intervention, and the control group (*n* = 500) will be referred to treatment by usual procedures. All patients complete a lifestyle questionnaire with the Alcohol Use Disorders Identification Test embedded as a case identification strategy. The primary outcome of the study will be health care expenditures 12 months after discharge. The secondary outcome will be the percentage of the target group, who 30 days after discharge, reports at the alcohol treatment clinics. In order to analyse both outcomes, difference-in-difference models will be used.

**Discussion:**

We expect to establish evidence as to whether The Relay Model is either cost-neutral or cost-effective, compared to referral by usual procedures.

**Trial registration:**

https://register.clinicaltrials.gov/by identifier:

RESCueH_Relay NCT02188043 Project Relay Model for Recruiting Alcohol Dependent Patients in General Hospitals (TRN Registration: 07/09/2014)

## Background

Compared to other countries the Danish population has a large intake of alcohol per capita, and almost all adolescents and adults in Denmark drink alcohol [1]. It is estimated that approximately 20 % of the adult population are heavy drinkers consuming >14/21 drinks/week (women/men), 14 % have a harmful alcohol use, and 3 % are dependent drinkers [2]. In Denmark the vast majority of services offered to patients suffering from alcohol use disorders are publicly funded and provided by a highly diverse group of about 60 specialized outpatient clinics, treating nearly 16,000 patients per year [3]. This is a small fraction of the estimated 140,000 alcohol dependent Danes [2], who needs specialized alcohol treatment.

Alcohol use disorders are associated with considerable societal costs and welfare losses to the Danish population. Annual societal costs include excess health care consumption, income loss compensations, children and youth intervention costs [3], production loss due to alcohol related short and long-term inability to work and premature death [4], and costs of alcohol related criminal activity and traffic accidents [5].

Carefully designed prevention and treatment interventions for alcohol use disorders can, if put into scale, help thousands of Danes and in addition generate economic benefits in terms of savings in the costs to society, listed above. Even if specialized treatment delivery itself is costly, it may generate sufficient savings to become cost-effective and perhaps even net-cost-saving [6]. A first approach may be to identify and recruit patients from general hospitals.

Alcohol use disorders are responsible for considerable physical morbidity and accidents, and many patients with alcohol problems are admitted to the general hospitals [7, 8]. In a systematic review of hospital screening studies the proportion of inpatients with alcohol use disorders was found to range between 16 and 26 % [9]. The prevalence is influenced by many factors: e.g. patient population, definitions, and assessment methods. The prevalence of dependence, determined by a diagnostic instrument, among patients in general hospitals is very high [10].

The incidence of patients with alcohol-related diseases is greatest in the departments receiving patients with the following conditions: falls, collapse, head injuries, assaults, gastrointestinal problems, unwell, neurological-psychiatric problems, cardiac symptoms and accidents [11, 12]. In Denmark such patients will typically be admitted to gastrointestinal (liver disease, oesophagitis, gastritis, pancreatitis), neurological (including seizures, head injure, stroke, peripheral neuropathy and vascular disease) and orthopaedic departments (falls, assault, accidents).

Many studies have examined brief interventions for patients in general hospitals [13–15], but it is not well established if alcohol dependent patients benefit from the interventions [16]. A more intensive and prolonged treatment delivered by specialists seems to be needed for the patient group suffering not only from problem drinking, but from alcohol dependence as well [17–20].

In studies on recovery from alcohol use disorders, health problems and hospital admission were among the most cited predictors of recovery [21]. Patients with alcohol use disorders admitted to general hospitals seem much more likely to be motivated for change than a comparable group of alcohol dependent patients in the community [22]. Individuals hospitalized with alcohol use disorders, even just assigned to control groups with no other intervention than assessment, seems significantly more often to remain non-problem drinkers or abstinent after discharge, compared with patients stemming from general practice [23]. In other words; health problems and hospital admission could open a window for changing alcohol consumption. Therefore, general hospitals seem to be in an outstanding position to detect and refer individuals with alcohol use disorders to specialized alcohol treatment.

Several studies have shown that between 36 and 54 % of hospitalized patients do not engage in psychosocial treatment after discharge, and between 20 and 90 % will subsequently relapse back to renewed alcohol abuse [24]. Therefore, barriers to engage in treatment for alcohol use disorders seem to exist. The low number of successful referral rates from inpatient to specialized alcohol treatment represents missed opportunities for patient improvement and cost savings [25].

Lash et al. found that having a therapist complete an aftercare group therapy attendance contract with patients at the completion of inpatient treatment, resulted in significant greater aftercare adherence [26]. In another study, Lash et al. investigated whether a treatment contract drafted by the outpatient therapist at discharge, followed by feedback and reminders in the form of telephone calls and letters, increased the turnout for outpatient group treatment, when compared to a control group who were offered only a treatment contract, drafted by the outpatient therapist. The study showed that significantly more patients in the intervention group began outpatient treatment, and after 12 months significantly more patients in this group were still abstinent/drug-free [27].

The purpose of a referral model is to increase the proportion of patients with alcohol use disorders who start specialized alcohol treatment after being discharged from the hospital. In order to be implemented in the health care system, the model must show an impact on both outcomes for patients and on the overall cost to the health care system. Hence, studies on referral models need to include analyses of cost-effectiveness [28]. In the alcohol treatment field, only few publications describe the cost-effectiveness of treatment alternatives. In a study of an outpatient abuse program in the United States, patients were followed 18 months before and 18 months after starting treatment. After treatment was initiated, a decrease in consumption of health services by 26 % was found [29]. Holder also found a decrease in the use of health services after initiation of treatment [30].

There is a need for developing referral models which can ensure that patients with alcohol use disorders engage in and continue treatment of their addiction after discharge from general hospital. Contracts, prompts and reinforcement developed by Lash et al., are some of the more promising low-cost interventions for increasing participation in outpatient treatment [31]. Attending outpatient treatment is considered essential to successful recovery for patients with alcohol use disorders and it is considered cost-effective for health services. However, only few Danes with alcohol dependence receive outpatient treatment. There is a need to investigate whether a Danish referral model can increase recruitment of alcohol dependent patients from general hospitals to outpatient treatment. This in turn might reduce the economic burden on health care systems and other parts of society and improve the prognosis for the patients.

Inspired by the method of Lash and colleagues, we have developed a Danish referral model called The Relay Model which will address the challenge and establish better referral procedure for dependent drinkers. The purpose of the study is to evaluate The Relay Model in order to assess: i) cost-effectiveness, ii) efficacy and iii) overall societal cost impacts.

## Methods

The study will be conducted as a single-blind pragmatic randomized controlled trial. Patients who are enrolled in the study are included from gastrointestinal, neurological and orthopaedic departments at Odense University Hospital (urban area, serving a population of around 220,000 citizens) and at Aabenraa Hospital (located in rural area serving a population of around 110,000 citizens).

In order to identify the patients a self-report version of the Alcohol Use Disorders Identification Test will be used as a case identification strategy [12]. A completed questionnaire yields a possible score from 0 – to 40 points. According to the cut-off values in the Alcohol Use Disorders Identification Test, a score between 8 and 15 points will be in the hazardous drinking category equal to a medium risk and will benefit from a brief intervention. A score of 15–40 point in the Alcohol Use Disorders Identification Test puts the patient in a harmful drinking or physical dependency category equal to a high risk, where they will benefit from brief intervention and referral to specialist alcohol treatment service.

### Inclusion and randomization

The procedure for inclusion and randomization of the patients is shown in the flow chart (Fig. 1 in Appendix). As a part of standard procedures and quality management, all consecutive patients in the participating departments will be asked to complete a 27-item lifestyle assessment questionnaire concerning smoking, nutrition, exercise and alcohol. The questions on alcohol will include the ten questions in the Alcohol Use Disorders Identification Test. The staff hands out the questionnaire to all patients admitted to the participating departments. Hereafter, the staff collects and scores the questionnaires according to the recommendations [12]. The staff reports the scores to the alcohol treatment clinic, daily. According to randomization, the patient will be allocated to intervention group if the patient meets the following inclusions criteria:Not participated in any alcohol-specific treatment for alcohol use disorders in the previous 6 monthsNot psychoticMore than 18 years of ageHospitalized for a minimum of 24 hResident within the uptake area of the involved alcohol treatment clinicsWilling to participate in the studyCognitively and physically capable.

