### Allocation concealment

The random allocation sequence of days will be performed by a computer. The randomization will be blinded to the patients as well as the hospital staff. They will not know on which days the alcohol therapist will appear on the ward, clarifying that the sequence will be concealed until interventions are assigned.

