### Intervention group

An alcohol therapist will attend the departments on days randomly drawn by a computer. He/she will go through the collected questionnaires, and patients with a score of eight or more in the Alcohol Use Disorders Identification Test will be contacted. The therapist will inform the patients that he/she comes from the outpatient alcohol treatment clinic. The patient will be informed about the study and if he/she consents, the alcohol therapist performs the Relay Intervention including a brief intervention. The therapist will interact with the patient in a non-confrontational and patient-centred manner by using the technique from motivational interviewing [32]. For patients with a score of 16+ in the Alcohol Use Disorders Identification Test, the significance of continuing an outpatient aftercare treatment and suggestion of a contract and an appointment to the alcohol treatment clinic is discussed. The design of the attendance contract is inspired by Lash & Blosser [33], and contains options for attending the outpatient clinic. Finally, patients will be informed that they will most likely meet again; if the patient participates in the outpatient aftercare treatment and that they will receive two letters at two weeks intervals, offering a new appointment should they not meet in the outpatient clinic at the agreed time. The intervention is expected to last 20 min.

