### Control group

Patients in this group will receive the usual procedures from the department’s staff.

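### Consent is sought after allocation and only on therapist days, so the intervention group is selected in a way that the control group, as described, is not

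*Protocol article*

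**What the plan says.** The unit of randomisation is the day. Allocation concealment states: "The random allocation sequence of days will be performed by a computer". Intervention group adds: "An alcohol therapist will attend the departments on days randomly drawn by a computer".

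Entry to the intervention arm is conditional. Inclusion and randomization reads: "According to randomization, the patient will be allocated to intervention group if the patient meets the following inclusions criteria". The list that follows has seven items: no alcohol-specific treatment in the previous 6 months, not psychotic, age over 18, at least 24 h in hospital, residence in the uptake area, willingness to take part, and cognitive and physical capability.

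Consent comes at the therapist's visit: "The patient will be informed about the study and if he/she consents, the alcohol therapist performs the Relay Intervention". The therapist works from the questionnaires on the ward: "He/she will go through the collected questionnaires, and patients with a score of eight or more" are contacted.

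The Control group section is one sentence: "Patients in this group will receive the usual procedures from the department’s staff". It mentions no approach, consent or eligibility check. Baseline data limits recruitment data to the AUDIT and a few demographic items. Follow-up is through national registers. The Analysis section plans a crude chi-square test on attendance and difference-in-difference for costs.

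**The concern.** Randomising days protects the comparison only if the patients counted in each arm are picked by the same rule whichever kind of day they met. As written, a patient who declines on a therapist day does not enter the intervention group, while a patient who would have declined on a control day is never asked and so cannot be left out.

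Willingness to talk to an alcohol therapist plausibly predicts both attendance at the clinic and later costs. The article itself treats motivation during a hospital stay as the opening that the model exploits. The attendance comparison is the more exposed of the two, because the chi-square test is unadjusted. For costs, difference-in-difference removes a gap that is the same before and after admission. It does not remove a difference in motivation to change, which would act on the trend.

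A second, weaker route is length of stay. The text shown does not say which allocation holds for a patient whose stay covers both kinds of day.

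**Working it through.** **1. The plan's own figure.** Inputs from Power calculation: mean additional cost 88,067 DKK, SD 144,967 DKK, reduction 26%, 80% power, about 500 per group. The target is 0.26 × 88,067 = 22,897 DKK, as stated. With n = 2(z_α + z_β)² SD²/Δ², a one-sided 5% test gives 496 per group, which matches 500. A two-sided 5% test gives 630. The article states neither the level nor the sidedness, so both are carried below. With 500 per group, SE = 144,967 × √(2/500) ≈ 9,169 DKK, and power is 80.3% (one-sided) or 70.4% (two-sided).

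**2. Which criteria could be made symmetric.** Age, residence, 24 h stay, recent alcohol treatment and psychosis could be read for controls from the questionnaire or the registers. Willingness and capability could not: no one is described as asking controls, and the recruitment data hold neither item. The asymmetry that cannot be repaired from the data described is therefore in these two criteria.

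**3. Size of consent selection, costs.** Let c be the consent share and D the amount by which consenters would cost less than refusers regardless of treatment. Both are assumed, since the article gives neither. If controls are unselected, the spurious difference in an unadjusted comparison is (1 − c) × D. Rejection is at nominal two-sided 5%, with no true effect and 500 per group.

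| c | D (% of 88,067) | (1 − c) × D, DKK | % of 22,897 | Rejection |
|---|---|---|---|---|
| 0.8 | 10% | 1,761 | 8% | 5.4% |
| 0.8 | 25% | 4,403 | 19% | 7.7% |
| 0.8 | 50% | 8,807 | 38% | 16% |
| 0.5 | 10% | 4,403 | 19% | 7.7% |
| 0.5 | 25% | 11,008 | 48% | 22% |
| 0.5 | 50% | 22,017 | 96% | 67% |

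Under difference-in-difference, D is replaced by the change in the gap from before to after admission. If part of the gap was already there, the bias is smaller than tabulated. The article gives no basis for splitting D. If consenters cost more than refusers, the sign reverses.

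**4. Attendance.** The same form applies: (1 − c) times the gap in untreated attendance between consenters and refusers. At c = 0.8 that is one fifth of the gap. No attendance rate is given, so no figure is offered.

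**5. Length of stay (illustration of an inference).** If any therapist day during the stay led to the intervention arm, the chance of entry would be 1 − (1 − p)^L, for a share p of therapist days and a stay of L days. With p = 0.3 assumed, this is 30% for 1 day, 66% for 3 days and 92% for 7 days. With geometric stays of mean 4 days (assumed), mean stay would be 5.1 days in the intervention arm and 2.1 in the control arm. This could push costs the opposite way from step 3, so the net sign is unknown.

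**6. Price of keeping decliners.** If the full planned effect occurs in consenters and none in decliners, the effect by allocation is c × 22,897 DKK.

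| c | Effect, DKK | Power at 500, one- / two-sided 5% | n per group for 80%, one- / two-sided |
|---|---|---|---|
| 0.9 | 20,607 | 73% / 61% | 612 / 777 |
| 0.8 | 18,318 | 64% / 52% | 775 / 984 |
| 0.7 | 16,028 | 54% / 42% | 1,012 / 1,285 |
| 0.5 | 11,448 | 35% / 24% | 1,983 / 2,517 |

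These use the article's SD in a plain comparison of two means.

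**The case against.** The inclusion procedure is said to be in a flow chart that is not shown, and the chart may apply the criteria to both arms. The list is headed as inclusion criteria, and its willingness item refers to the study as a whole, so it can be read as trial-level entry. The Control group sentence describes care, not membership. An article also commonly leaves the analysis set to a fuller document.

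Much of this stands, and it limits the point. A reader might infer that all seven criteria separate the arms, but five could be applied alike to controls. A reader might infer that longer-stay, costlier patients do drift into the intervention arm. No passage says so, and the daily reporting of scores is compatible with assignment on the day of scoring. A reader might also take 30% refusal and a 0.25 SD gap, obtain 0.30 × 0.25 × 144,967 = 10,873 DKK, and conclude that bias equals 47% of the target. Both inputs are assumptions, and the sum counts the whole level difference as bias although the planned analysis removes its time-constant part.

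The objection does not dispose of consent. The text itself makes willingness a condition of allocation to one arm and places the request at the therapist's visit. A chart could not make willingness observable in patients whom nobody asks, and no consent step common to both arms is described. An intention-to-treat rule in an unseen plan would not help if decliners never enter the arm.

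**Conclusion.** The point holds for consent and capability. Followed as written, the plan compares patients who agreed after allocation with controls for whom no such step is described. This affects the attendance comparison directly, and the cost comparison to the extent that the selected difference changes over time.

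The documents fix neither size nor direction. At an assumed 80% consent and cost gaps of 10-50% of the stated mean, the unadjusted bias is about 1,800-8,800 DKK (8-38% of the target). It is less under difference-in-difference where the gap predates admission. Selection by length of stay is possible, because the text shown gives no index-day rule, but it remains an inference. The documents do not support saying that the cost result is confounded by a known amount, or by eligibility as a whole. They do support requiring a stated rule for both arms before the data are analysed.

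**What to change.** - Assign each patient's arm by the randomised status of one index day, for example the day the questionnaire is first scored 8 or more, whatever days follow.
- Define the analysis population in both arms only by criteria that can be read identically from the questionnaire or registers: AUDIT score, age, residence, 24 h stay, alcohol treatment in the previous 6 months, psychosis diagnosis.
- Make the primary analysis, for costs and for attendance, all such patients by index-day allocation, including decliners and those the therapist did not reach. Keep willingness and capability as conditions for delivering the intervention, not for being counted.
- Report consenters only in a secondary, complier-type analysis.
- Restate the power for this analysis set, with the significance level, sidedness and an assumed consent share.

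The wording change is small, but the consequences are not. Permission for register linkage must cover decliners and unreached patients. Keeping them also dilutes the effect: at 70% consent, restoring 80% power needs about 1,012 (one-sided 5%) or 1,285 (two-sided 5%) per group. If recruitment cannot be extended, the lower power should be stated openly.

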### Allocation concealment

The random allocation sequence of days will be performed by a computer. The randomization will be blinded to the patients as well as the hospital staff. They will not know on which days the alcohol therapist will appear on the ward, clarifying that the sequence will be concealed until interventions are assigned.

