### Power calculation

In the absence of data from general hospitals, we use data for the power calculation stemming from the study by Parthasarathy et al., who found that outpatient treatment decreased the consumption of health services by 26 % [29]. Primary outcome is the socio-economic costs of alcohol-abuse patients. Based on information from the Danish Institute of Governmental Research we have an estimate of the average total additional expenses for alcohol abuse patients of 88,067 DKK. Treatment for alcohol dependence is expected to lower the additional costs by 26 %. Since the individual excess costs of patients is highly variable with a standard variation of 144,967 DKK, the coefficient of the variation is quite high. Therefore, the power calculation results in a total of about 500 patients in each of the two groups in order to be able to detect the average decrease in total additional expenses of 22,897 DKK, with 80 % probability.

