### Analysis

The primary outcome, health care expenditures, will be calculated in two parts. First, a chi-square test will be used to do a crude comparison of the attendance rates of the two groups (intervention and control). Second, health care costs differences will be measured and tested using difference-in-difference analysis. The secondary outcome, societal costs, will also consist of two parts. First, the effect; a marker of reduced alcohol consumption after 12 months (i.e. alcohol related health care contacts), will be assessed in a difference-in-difference analysis. Second, the societal costs will be analysed like health care costs. Cost data are non-Gaussian and non-linear statistical models and bootstrapping techniques will be used in the statistical analyses.

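### Days are randomised, but the attendance test and the sample size treat patients as individually randomised; the likely effect is small

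*Protocol article*

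**What the plan says.** Under Allocation concealment, the protocol article states: "The random allocation sequence of days will be performed by a computer". The Intervention group section says how the day sets the arm: "An alcohol therapist will attend the departments on days randomly drawn by a computer". On those days the therapist goes through the collected questionnaires and approaches patients scoring eight or more. The Inclusion and randomization section, by contrast, writes as if patients were the units randomised.

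The Power calculation section works from patient-level figures. The starting point is "average total additional expenses for alcohol abuse patients of 88,067 DKK", and the variability is given as "the individual excess costs of patients is highly variable with a standard variation of 144,967 DKK". About 500 patients per group are said to be enough to "detect the average decrease in total additional expenses of 22,897 DKK", "with 80 % probability". It gives no number of days, patients per day, ICC or design effect.

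For attendance, the Analysis section says that "a chi-square test will be used to do a crude comparison of the attendance rates of the two groups". Costs are to be analysed by difference-in-difference, and for cost data non-linear models and "bootstrapping techniques will be used in the statistical analyses". The unit to be resampled is not given. The Abstract also names difference-in-difference for both outcomes.

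**The concern.** When a day is drawn, every eligible patient handled that day goes to the same arm. The day is then the unit of randomisation, and patients are observations within it. Patients of the same day may resemble each other: they are approached in the same visit, under the same ward conditions, and within an arm their exposure is shared. If so, 500 patients carry less information than 500 independently randomised ones.

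Two stated elements of the plan do not allow for this. The chi-square test takes its variance from independent patients, and the sample size uses the patient-level standard deviation with no inflation. With a positive within-day correlation, both err in the same direction: type I error for attendance is above nominal, and power is below the figure claimed. Attendance is the outcome most plausibly affected, because the same-day contact with the therapist acts on it directly.

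**Working it through.** **Inputs from the protocol article.** Difference 22,897 DKK (0.26 × 88,067 = 22,897.4); standard deviation 144,967 DKK; 80 % power; about 500 per arm (Power calculation). Recruitment from 1 November 2013 to summer 2016 (Recruitment). Total 1,000 patients (Abstract).

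**Assumptions.** Alpha is not stated, so 5 % is used. Summer 2016 is taken as 1 June to 31 August. The ICC is not given; 0.01 to 0.05 is used as the main range. Every day is taken to belong to one arm or the other.

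**Step 1: reproduce the stated size.** For independent patients, n per arm = 2 × (z_alpha + z_power)² × (SD/difference)².

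- (144,967 / 22,897)² = 40.09.
- One-sided 5 %: 2 × (1.645 + 0.842)² × 40.09 gives 496. This matches about 500; power at 500 is 80.3 %.
- Two-sided 5 %: 2 × (1.960 + 0.842)² × 40.09 gives 630. This does not match; power at 500 is 70.4 %.

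So the stated size follows from the individual-patient formula with design effect 1.

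**Step 2: patients per day.** From 1 November 2013 to 1 June 2016 is 943 days, and to 31 August 2016 is 1,034 days. At 5/7 of these, weekdays number about 674 to 739.

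- Calendar days: 1,000/1,034 = 0.97 to 1,000/943 = 1.06 patients per day.
- Weekdays only: 1,000/739 = 1.35 to 1,000/674 = 1.48 patients per day.

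The mean is therefore about 1.0 to 1.5 per day over both hospitals.

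**Step 3: design effect (DE).** For equal clusters of size m, DE = 1 + (m − 1) × ICC. Day sizes will vary. If they are Poisson with mean λ, the patient-weighted mean size is 1 + λ, so DE = 1 + λ × ICC. The standard error is understated by the factor √DE. The true two-sided type I error is 2 × [1 − Φ(1.96/√DE)]. The required n is 496 × DE, and power is evaluated at 500/DE.

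| Patients per day | ICC | DE | Two-sided type I error | n per arm, one-sided | One-sided power at 500 |
|---|---|---|---|---|---|
| 1.0 (Poisson) | 0.01 | 1.010 | 5.1 % | 501 | 80.0 % |
| 1.0 (Poisson) | 0.05 | 1.050 | 5.6 % | 521 | 78.6 % |
| 1.48 (Poisson) | 0.01 | 1.015 | 5.2 % | 504 | 79.8 % |
| 1.48 (Poisson) | 0.05 | 1.074 | 5.9 % | 533 | 77.8 % |
| 1.48 (Poisson) | 0.10 | 1.148 | 6.7 % | 570 | 75.4 % |
| 5 (equal) | 0.05 | 1.20 | 7.4 % | 596 | 73.7 % |
| 10 (equal) | 0.05 | 1.45 | 10.4 % | 720 | 66.6 % |

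The first four rows are the range that the planned accrual supports. The fifth is a sensitivity value for the ICC. The last two need patients concentrated on fewer days than the accrual average suggests.

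**Step 4: a smaller cluster.** If each department had its own sequence of days, three departments at two hospitals, read as six, would see at most about 1.48/6 = 0.25 included patients per department-day. DE is then about 1 + 0.25 × 0.05 = 1.01.

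**The case against.** The strongest reply is that the effect is nearly nil. At one to one and a half patients per day, many days contribute a single patient, and clustering cannot matter where there is no cluster. The document gives no ICC, and nothing in it suggests that 12-month costs depend on the day of allocation. A therapist effect would run across days, so clustering by day would not capture it. This stands as an argument about size. It does not make a patient-level test the right match for a day-level allocation.

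The chi-square test is labelled crude, and the Abstract also names difference-in-difference for attendance. That weakens the claim that the chi-square test carries the inference. But it is the only attendance test that the Analysis section specifies.

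A reader might infer more than the document supports:

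- **That standard errors are certainly too small.** This needs a positive within-day ICC and days with more than one patient. The article states neither.
- **That type I error reaches about 9 % and power falls to about 57 %.** Those figures need 8 patients per day and an ICC of 0.05 together (DE 1.35), with power taken two-sided. The planned accrual points to far smaller days.
- **That clustering takes power from 80 % to 70 %.** That fall is the difference between a one-sided and a two-sided 5 % test at 500 per arm. It is a separate matter and larger than the plausible clustering loss.
- **That the cost analysis is wrong.** A bootstrap over patients would share the problem, but the resampling unit is simply not stated, and an analysis plan that is not shown may set it to the day. Omitting hospital and department from a crude comparison is likewise a matter of precision, not an error.

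**Conclusion.** The mismatch is real: days are randomised, while the stated attendance test and the stated sample size treat patients as independent units. Its consequence is conditional on outcomes correlating within day.

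At about 1.0 to 1.5 patients per day and an assumed ICC of 0.01 to 0.05, the design effect is about 1.01 to 1.08 and standard errors are about 0.5 to 3.6 % too small. Two-sided type I error is about 5.1 to 5.9 %, and one-sided power about 78 to 80 % against 80.3 %. Bunching raises this: five patients per day at ICC 0.05 gives a design effect of 1.20 and 73.7 % power. The range rests on the accrual average, Poisson-varying day sizes and an ICC that the document does not supply.

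Severity is minor to moderate. The change is worth making because it costs almost nothing and aligns the analysis with the design, not because the results are likely to be seriously distorted.

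**What to change.** 1. State in the design and Inclusion and randomization sections that the day is the unit of randomisation, and whether one draw covers all departments or each department has its own sequence. If the latter, the department-day is the cluster.
2. Replace the plain chi-square test for attendance with one that respects the day, for example a logistic GEE clustered on day or a comparison with day-clustered robust variance. With several hundred days, such estimators should behave well.
3. Use the same clustering for the cost difference-in-difference, and have the bootstrap resample whole days. If the analysis plan already does so, a sentence in the protocol is enough.
4. Restate the power with the expected patients per day, the assumed ICC and the resulting design effect.

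**Cost.** Intervals become slightly wider and the stated power slightly lower; to keep 80 % one-sided power, the size at the accrual-based range would be about 501 to 533 per arm. No change to patient contact is needed. Each patient's allocation day must be in the analysis file; since ward staff report scores to the clinic daily, it should be recoverable.
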